## Methods

### Design

This protocol describes a feasibility study of a prospective, assessor-blinded, randomised clinical trial with two parallel groups and a 12-week intervention period (Fig. 1). Participants will be randomised to each group using a 1:1 ratio (see ‘Allocation’ for more detail regarding randomisation). The primary end point is 12 weeks. The trial will be conducted in physiotherapy clinics in Brisbane, Australia and The University of Queensland. This study protocol follows the Standard Protocol Items: Recommendations for Interventional Trials (SPIRIT) guidelines [23]. The trial was prospectively registered with the Australia and New Zealand Clinical Trial Registry on 11th July 2019 (ACTRN12619000987167; http://www.ANZCTR.org.au/ACTRN12619000987167.aspx).

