#### Secondary outcome measures

In the absence of a defined core outcome set for PHP, we will record a comprehensive set of measures that are likely to capture all health related domains of PHP. For example, we will record record a numeric rating scale for first step pain, worst pain and average pain to ensure we are covering the pain aspect of PHP. We will use the Foot and Ankle Ability Measure to capture the disability; the Foot Health Status Questionnaire to evaluate quality of life; the Pain Self-Efficacy Questionnaire to get a sense of the psychological aspects; the Active Australia Survey to gauge how active the participants are; and we will capture foot muscle morphology, foot posture index, foot mobility, toe flexion strength, ankle dorsiflexion, and ankle plantarflexor strength to gain a representation of structural and functional aspects of PHP. These feasibility/practicality of use, response profile (effect size), and completion rates will be used to guide decisions in future trials. For participants with bilateral pain, the foot that the participant reports as having the worst symptoms will be evaluated.

Patient-reported outcome measures will be used to evaluate pain, physical function, physical activity level and pain self-efficacy.

*Pain severity:* An 11-point numerical rating scale anchored by 0 (no pain at all) and 10 (worst pain imaginable) will be used to rate first step, worst and average level of pain that the participant has experienced in the past week [26]. The numerical rating scale is reported to be more responsive, easier to administer and preferred by patients compared to other pain scales [27]. A 2-point change is reported to be a clinically important difference in individuals with chronic pain [26].

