### Sample size

Due to the exploratory nature of this novel research with the use of MRI and within funding constraints, a sample size of 20 participants (10 per group) will be enrolled into this feasibility study. Sample sizes of this magnitude will best provide estimate parameters for determining a clinical trial that seeks to identify large standardised effect sizes [50].

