### Statistical analysis

Data will be analysed on an intention-to-treat basis. Primary outcomes will be presented as descriptive statistics. To explore treatment effects *(secondary aim)*, descriptive data (group means, standard deviation) and mean differences (95% confidence intervals) for within and between-group comparisons will be reported. To provide an indication of the magnitude of observed differences, standardised mean differences (mean difference / pooled standard deviation) will also be calculated. Changes within and between groups will be considered in relation to reported scores of meaningful change and measurement error. The descriptive data and point estimates of treatment effects reported from this study will be used to calculate the required sample size for a full-scale RCT.

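### Treatment-effect point estimates from 10 per arm are too imprecise to size the full-scale RCT; take the SD from this study, but not the effect

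*Protocol article*

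**What the plan says.** The Sample size section states that "a sample size of 20 participants (10 per group) will be enrolled into this feasibility study". The reasons given are the exploratory aim, the use of MRI and funding. It adds: "Sample sizes of this magnitude will best provide estimate parameters for determining a clinical trial that seeks to identify large standardised effect sizes". It gives no number for a large effect and no precision calculation.

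The Statistical analysis section plans group means and SDs, mean differences with 95% confidence intervals, and "standardised mean differences (mean difference / pooled standard deviation) will also be calculated". Published scores for meaningful change and measurement error are to help interpret the observed changes. The section then ends by naming two inputs for the next trial's sample size: the descriptive data, and the effect estimates ("point estimates of treatment effects reported from this study will be used to calculate the required sample size for a full-scale RCT"). The Discussion repeats more loosely that the results will inform that calculation.

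Under Secondary outcome measures, after noting that no core outcome set exists, the protocol says: "These feasibility/practicality of use, response profile (effect size), and completion rates will be used to guide decisions in future trials". The same section cites important-change values: 2 points for pain, 8 and 9 for the two Foot and Ankle Ability Measure subscales, and 14, 7 and 9 for the three Foot Health Status Questionnaire subscales. None of these is tied to the sample size of the full-scale trial.

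**The concern.** A sample size formula needs a target difference and a measure of variability. Ten per arm gives a usable, if rough, SD. It gives almost no information about the size of the treatment effect. Required n varies with the inverse square of the effect, so the error in the estimate is magnified. A chance high estimate produces a trial too small to detect the real effect. A chance low one produces an unaffordable trial or none at all. Informing the full-scale RCT is this study's declared purpose, so the rule for handing over its results matters even though treatment effects are only a secondary aim here.

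**Working it through.** **Inputs from the protocol:** 10 per group; 1:1 allocation ("Participants will be randomised to each group using a 1:1 ratio"); SMD = mean difference / pooled SD; pooled SD on 10 + 10 - 2 = 18 degrees of freedom. **Assumed, because not stated:** two-sided 5% level, 80% power, all 20 participants measured, true SMD of 0.3, 0.5 or 0.8 (the last standing for a large effect), and the outcome SDs used in step 6.

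1. *The plan's own figure.* The 20 is simply 2 × 10. No alpha, power, difference or SD lies behind it, so there is nothing further to reproduce.

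2. *Precision.* SE(d) = √(2/10 + d²/40). At d = 0 this is 0.447; at d = 0.8 it is √(0.2 + 0.016) = 0.465. The 95% CI for an observed 0.8 is 0.8 ± 1.96 × 0.465, or -0.11 to 1.71 (noncentral t: -0.12 to 1.70).

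3. *What that interval means for n.* The two-sample t-test needs 176 per arm at SMD 0.3, 64 at 0.5, 26 at 0.8 and 7 at 1.7. At or below zero no finite n exists. One large observed effect is therefore compatible with anything from a tiny trial to none.

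4. *How often n is badly wrong, one prespecified outcome.* By the normal formula, planned n = 2 × (1.96 + 0.84)² / d² = 15.7/d². Apart from rounding, planned n is below half the right n when d exceeds √2 times the true value, and above twice it when d is below the true value divided by √2. Simulating the observed SMD at 10 per arm gives:

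| True SMD | Right n per arm (normal formula) | Below half | Above twice, or no usable n | Wrong by more than twofold |
|---|---|---|---|---|
| 0.3 | 175 | 40% | 42% | about 82% |
| 0.5 | 63 | 33% | 37% | about 70% |
| 0.8 | 25 | 25% | 30% | about 55% |

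Replacing the normal formula by the t-test and the simulation by the noncentral t distribution gives 81%, 69% and 51%. At a true 0.5 the middle half of planned sizes runs from 24 to 399 per arm.

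5. *Conditional on choosing the outcome by observed effect.* Suppose the largest of five outcomes were taken, each with true SMD 0.5 and correlation 0.5 between them (all assumed). The mean selected SMD would be 0.94 and the median planned n 19 per arm, against 63 needed. About 68% of plans would fall below half the needed n and about 8% above twice it.

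6. *Taking only the SD from this study.* With the target difference fixed, the chance of a more than twofold error falls to about 4% to 5%. The upper one-sided 80% limit for the SD is √(18/12.86) = 1.18 times the estimate, which raises n by 1.18² ≈ 1.40. For a 2-point pain difference at an assumed SD of 2, 2.5 or 3, the t-test needs 17, 26 or 37 per arm, and 23, 36 or 51 with the inflated SD.

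**The case against.** The strongest reply is that this is a feasibility study, that its size is openly set by funding, and that its primary outcomes are feasibility, credibility and acceptability. The sentence at issue names the descriptive data as well as the effect estimates, confidence intervals will be reported, and meaningful-change scores are used in interpretation. All of that is correct. Ten per arm is not in itself a fault, and the SDs are a proper input. What remains is that effect point estimates are also named as an input, and nothing in the protocol ties the sizing to a confidence limit, to shrinkage or to an important difference.

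Three stronger readings are tempting and are not supported:

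- *The next trial will be built on the most flattering outcome.* The protocol lists effect size as one of three guides, beside practicality and completion, and speaks of future decisions in general. It has no rule to pick the largest effect. Many of the measures are physical ones meant to explore mechanisms.
- *The next trial will be underpowered.* With one prespecified outcome the error runs both ways. A one-sided conclusion needs an added assumption, such as a rule to proceed only above some observed effect, and the protocol gives none.
- *The SMD formula is itself materially biased.* The small-sample correction at 18 degrees of freedom is 1 - 3/71 = 0.958. That is about 4%, negligible beside a standard error near 0.45.

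**Conclusion.** The point holds for the use of effect point estimates, and only for that. Even at the large effect the Sample size section has in mind, the rule would miss the right n by more than a factor of two in just over half of pilots, and more often at smaller effects. The direction cannot be predicted unless outcomes are also chosen by observed effect, which the protocol leaves open but does not prescribe. The percentages assume 80% power, a two-sided 5% level, an unadjusted two-group comparison and complete follow-up; dropout would make the estimates less precise still. This should be fixed, but it is not critical. It affects the planning of a later trial, which will need its own justification, and leaves this study's conduct and primary results untouched.

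**What to change.** Replace the last sentence of Statistical analysis with wording to this effect: *The full-scale RCT will be sized on an important between-group difference for a primary outcome chosen on clinical importance, completeness and practicality. This study will supply the SD, with an allowance for its uncertainty, the baseline-to-follow-up correlation, attrition and adherence. Effect estimates will be reported with 95% confidence intervals as exploratory and will not be used for sizing.*

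The values cited under Secondary outcome measures are the natural starting point. The protocol presents the 2-point pain value as a change, so its use as a between-group target must be justified. An upper one-sided 80% limit is one reasonable allowance for the SD; other conventions would serve. In Secondary outcome measures, add that observed effect size will not be used to select the primary outcome.

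The change is wording only and is still possible although follow-up has finished, because it concerns the next trial. The cost is a possibly larger full-scale trial: for 2 points on the pain scale at an assumed SD of 2.5, about 36 per arm instead of 26.

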## Discussion

PHP is a recurrent and persistent musculoskeletal condition that affects a wide range of individuals. The burden of the condition is significant with low physical activity levels, poor quality of life and higher rates of stress, anxiety and depression [2, 9]. Current evidence to guide selection of treatment options for PHP is limited, with several systematic reviews reporting that treatment effects are small, ineffective when compared to placebo or of short duration only (1–6 weeks) [51–54]. In terms of IFM exercise for PHP, only three superiority trials have been conducted and results provide little evidence to guide the use of exercise for PHP.

Our feasibility study of a prospective assessor-blinded randomised clinical trial will be the first to evaluate the feasibility of a full-scale RCT, as well as treatment response, of a progressive foot focused exercise plus education intervention for the management of PHP, when compared to a wait and see approach (brief advice). The FEET trial will address several limitations of previous investigations, such as exercise programmes with insufficient training volume and intensity, number of exercises, lack of progression and integration to functional positions. The exercise program in this study was developed based on existing biomechanical studies that have reported the function of the IFMs during walking and running [11–13]. Accordingly, the exercises are designed to train the foot for these functional requirements. For example, our program will incorporate varied contraction types (i.e. isometric, concentric and eccentric); functional weight bearing positions; progressive loading via seated, two-leg or single-leg weight bearing or increasing resistance tubing; incorporation of functional tasks (e.g. calf raise to mimic propulsion and squat to mimic stance phase absorption) and rate of loading (e.g. jumping and hopping). The exercise program has been refined through pilot investigations and feedback from individuals with PHP and physiotherapists practicing in the Brisbane region. A novel feature of the FEET trial is the inclusion of a comprehensive set of physical measurements (including IFM morphology), which will help to explore potential mechanisms of effect, whereas existing investigations have focused solely on patient-reported outcomes. An improved understanding of potential mechanisms of effect is a preliminary step towards identifying individuals that may be more suited to this approach.

Although methodological factors have been incorporated into the design of the study to minimise bias (e.g. randomised group allocation via concealed allocation and outcome assessment by a blinded assessor), there are some sources that could not be addressed. For example, it is not possible to blind the participants or the treating physiotherapists to the allocated groups due to the nature of the interventions. We also acknowledge the potential for performance bias due to the structure of the interventions and different contact time with the treating physiotherapist (i.e. one treatment session versus eight treatment sessions). We selected our comparator group (brief advice) to best reflect a wait-and-see approach, given the lack of studies in the literature that compare interventions for PHP to a wait-and-see or minimal intervention. The ‘brief advice’ provided is deliberately intended to provide minimal information for that reason.

The trial will be reported in accordance with the CONSORT statement. The results of this feasibility trial will inform the development of a full-scale RCT including the calculation of required sample size. Future high quality RCTs are required to identify effective interventions for PHP and improve the management of this recurrent and persistent condition.

### Trial status

The study was registered on 11 July 2019. Enrolment of the first participant was 2 August 2019. Data collection commenced on 2 August 2019. The final follow-up measurement was conducted on 31 January 2020.

## Data Availability

Data sharing not applicable to this article as no data-sets were generated or analyzed during the current study.

## Abbreviations

CONSORT: Consolidated Standards of Reporting Trials
FEET Trial: Foot Exercise and Education for the Treatment of plantar heel pain
ICC: Intra-class correlation coefficient
IFMs: Intrinsic foot muscles
MDC: Minimal detectable change
MRI: Magnetic resonance imaging
PHP: Plantar heel pain
SEM: Standard error of measurement
SPIRIT: Standard Protocol Items Recommendations For Interventional Trials
